## Abstract

This study protocol aims to investigate how localised cooling influences the skin’s microvascular, inflammatory, structural, and perceptual tolerance to sustained mechanical loading at the sacrum, evaluating factors such as morphology, physiology, and perceptual responses. The protocol will be tested on individuals of different age, sex, skin tone and clinical status, using a repeated-measure design with three participants cohorts: i) young healthy (n = 35); ii) older healthy (n = 35); iii) spinal cord injured (SCI, n = 35). Participants will complete three testing sessions during which their sacrum will be mechanically loaded (60 mmHg; 45 min) and unloaded (20 min) with a custom-built thermal probe, causing pressure-induced ischemia and post-occlusive reactive hyperaemia. Testing sessions will differ by the probe’s temperature, which will be set to either 38°C (no cooling), 24°C (mild cooling), or 16°C (strong cooling). We will measure skin blood flow (via Laser Doppler Flowmetry; 40 Hz); pro- and anti-inflammatory biomarkers in skin sebum (Sebutape); structural skin properties (Optical Coherence Tomography); and ratings of thermal sensation, comfort, and acceptance (Likert Scales); throughout the loading and unloading phases. Changes in post-occlusive reactive hyperaemia will be considered as the primary outcome and data will be analysed for the independent and interactive effects of stimuli’s temperature and of participant group on within- and between-subject mean differences (and 95% Confidence Intervals) in peak hyperaemia, by means of a 2-way mixed model ANOVA (or Friedman). Regression models will also be developed to assess the relationship between absolute cooling temperatures and peak hyperaemia. Secondary outcomes will be within- and between-subject mean changes in biomarkers’ expression, skin structural and perceptual responses. This analysis will help identifying physiological and perceptual thresholds for the protective effects of cooling from mechanically induced damage underlying the development of pressure ulcers in individuals varying in age and clinical status.

## Introduction

Pressure ulcers (PUs) are localised damage to the skin and sub-dermal tissues, resulting from sustained periods of pressure, or pressure in combination with shear forces [1]. In the United Kingdom alone, the annual cost of treating chronic wounds, including PUs, has been estimated at £8.3 billion [2]. Accordingly, an improved understanding of the fundamental mechanisms underlying the physiological tolerance of human skin to mechanical loading could lead to the development of cost-effective, personalised solutions to prevent these wounds and improve patient care and quality of life.

Sustained localised mechanical loading on the skin can arise from lying and sitting postures, as well as the prolonged attachment of medical devices, e.g. prosthetics or respiratory masks [3, 4]. Internal tissue deformations will occur as a result of sustained pressure and shear forces that can lead to changes in the physiology of skin and sub-dermal tissue, including ischemia in the blood vasculature, lymphatic impairment, and direct deformation damage [5]. When load is removed, ischemia reperfusion injury may also occur due to the onset of post-occlusive reactive hyperaemia [6]. Reactive hyperaemia can increase the risk of ischemia reperfusion injury by triggering the release of oxygen-derived free radicals with cytotoxic effects, and this can play a role in the pathophysiology of PUs [7]. In addition, microclimate conditions within and around skin tissues strongly influence its tolerance to mechanical loading. For example, elevated temperature and humidity at the skin interface reduces the mechanical stiffness and strength of the skin and can increase its friction coefficient [4]. In contrast, cooling reduces skin tissue’s metabolic demands and could increase the skin’s physiological tolerance to mechanical damage [4, 8].

Evidence that changes in skin temperature could play a role in the tolerance of the skin to mechanical loading and shear came from early animal studies using porcine models, revealing that reduced skin temperature minimises the risk of PU formation through altered microvascular responses [9, 10]. More recently, the protective effective of reducing skin temperature has been demonstrated in rats [11, 12]. While this evidence highlights the potential therapeutic role of skin cooling for protecting tissue health, the mechanisms by which cooling enhances skin tolerance to pressure remain poorly understood in humans [9–11, 13–16]. Specifically, it remains unclear whether and to what extent the benefits of lowering skin temperature arise from the individual or combined effects of: 1) preserved microvascular function during mechanical loading and/or attenuated post-occlusive reactive hyperaemia following on pressure release; and 2) downregulation of skin’s inflammatory responses to sustained mechanical pressure. Animal studies revealed that local cooling, as well as the stimulation of cold sensitive TRPM8-expressing neurons in dorsal root ganglions, could modulate the skin’ inflammatory responses to acute mechanical stress (e.g. pressure loading) [12] and chronic skin damage (e.g. chronic dermatitis) [17], via downregulation of the expression of pro-inflammatory cytokines such Tumour Necrosis Factor alpha (TNF-α).

In addition to its physiological effects, it is well known that localised cooling of the skin can induce cold discomfort, which, if the magnitude of the cooling stimulus is large enough, can limit acceptability and adherence to therapeutic interventions designed to maintain skin health, particularly for vulnerable individuals at risk of PUs such as the elderly [18]. Hence, cold-induced discomfort could provide an obstacle for the adoption of skin cooling as a therapeutic intervention to promote skin integrity in humans. However, there is limited evidence on how the absolute cooling temperature and applied pressure on the skin interact in driving discomfort [19]. Despite these challenges, several support surfaces and therapeutic interfaces have been designed with local and full body cooling applied through microclimate management systems [20–22], although the evidence underlying their efficacy remain limited.

Modelling the relationship between the physiological and perceptual effects of skin cooling could provide an empirical approach to identify a common level of cooling that proves both physiologically beneficial and perceptually acceptable. This could then be translated to inform design parameters for more effective support surfaces and therapeutic interfaces.

It should also be recognised that the underlying tolerance to pressure at the skin interface, as well as the physiological and perceptual effects of cooling to pressure-induced damage, may vary as a function of age and comorbidities [3]. These states are associated with changes in skin biophysics and morphology [23], and in thermoregulatory and perceptual sensitivities. For example, ageing is likely to modulate the effects of cooling on tissue tolerance, as aged skin presents a reduced physiological and perceptual sensitivity to cold, due to decreases in both reflex cutaneous vasoconstriction, and density of thermoreceptors [24]. Similarly, the presence of a spinal cord injury (SCI) is associated with autonomic (e.g. impaired control of skin blood flow) and sensory dysfunctions (e.g. perceptual loss below injury level) [25, 26]. Thus, there may be variations between reductions in cold sensitivity and diminished efficacy of therapeutic cooling associated with age and comorbidities.

This study protocol aims to investigate: 1) how different levels of localised cooling influences the skin’s microvascular, inflammatory, structural, and perceptual responses to sustained mechanical loading at the sacrum; and 2) how aging and spinal cord injury may modulate the metabolic, immunological, biophysical, and perceptual pathways underlying the beneficial effects of localised cooling on skin tolerance to mechanical loading. To achieve our aims, we have designed a clinically relevant experiment in healthy young participants and in groups at-risk of PUs (i.e., older and SCI), as detailed in the sections below. The investigation will offer a combination of skin viability, thermal physiology, and non-invasive skin sensing technologies, to develop new basic knowledge on the role of temperature in reducing the risk of skin damage. This will support innovation in the design of healthcare and user-centred technologies, such as mattresses, clothing, and medical devices that can safely interface with the skin and provide some protection from damage. This will unlock the potential of cooling to the skin that will help maintain skin health across the life course.

## Materials and methods

### Overview

Participants will attend the laboratory within the Clinical Academic Facility located at Southampton General Hospital (Southampton, UK), to complete three experimental sessions separated by a minimum of 24 hrs. During the sessions, participants’ skin over the sacrum will be mechanically loaded (60 mmHg; 45 min) and unloaded (minimum tare load: 17.5 mmHg; 20 min) with a custom-built thermal probe, to cause pressure-induced ischemia and post-occlusive hyperaemia. The study will be a randomised cross-over design, involving three probe temperatures, which will be set to either 38°C (no cooling), 24°C (mild cooling), or 16°C (strong cooling). An overview of the study design can be found in Fig 1.

**Fig 1 pone.0303342.g001:**
[figure not shown]
Experimental design. We have designed a clinically relevant experiment in healthy young participants and in groups at-risk of PUs (i.e., elderly and spinal cord injured, SCI), which will determine how different levels of cooling [i.e. no cooling (38°C), mild cooling (16°C), and strong cooling (16°C)] alter the skin’ microvascular, inflammatory, structural, and perceptual responses to sustained pressure-induced ischemia and reactive hyperaemia. From an applied standpoint, the research will identify physiological and perceptual cooling thresholds (i.e. level of cooling, modulations via age and clinical status), which could be used as design parameters for the development of user-centred medical devices and thermal wearables. LDF: Laser Doppler Flowmetry; OCT: Optical Coherence Tomography.

### Participants

Three participant cohorts will be recruited: i) young healthy (n = 35); ii) older healthy (n = 35); and iii) spinal cord injured (SCI, n = 35). Sample size calculations were performed using Gpower (Gpower 3.1) with an effect size f = 0.4 for a repeated-measure ANOVA [parameters: within-between interaction; α = 0.05; β = 0.80; 3 groups; 3 measurements (i.e. peak hyperaemia at 38, 24, 16°C)], based on published data on the mean difference in peak hyperaemia (expressed as percentage of maximal cutaneous vascular conductance, CVCmax) during control conditions (32.7 ± 9.4% CVCmax) and during sensory nerve block (17.3 ± 6.8% CVCmax) [27]. Changes in peak hyperaemia were identified as the primary experimental outcome, as this represents a robust and repeatable microvascular response. The effects of cooling on peak hyperaemia are likely to be similar to those of cutaneous sensory nerve bloc [27], given that cooling also impairs the activity of cutaneous sensory nerves [28]. Hence, it was identified that the 50%-reduction in peak hyperaemia reported by Lorenzo and Minson [27] was a large (f = 0.4) and physiologically meaningful effect size to evaluate the beneficial effects of cooling on sustained mechanical loading. Based on the data above, we estimated a minimum sample size of 18 participants per group, and we propose testing of 35 individuals per group to allow for sufficient statistical power and to account for up to 50% dropout. Participants will be recruited according to the criteria in Table 1.

**Table 1 pone.0303342.t001:** Participant inclusion and exclusion criteria.

Inclusion	Exclusion
18–70 years old (young healthy 18–35 years old; older healthy 55–70 years old).	Young and older health groups only (does not apply to SCI group, see text below): suffering from cardiovascular, metabolic, and neurological disorders and/or comorbidities, e.g., hypertension, diabetes, chronic lung disease.
Male or female (minimum 17 for each sex).	Raynaud’s disease.
Skin tone dark, medium, or light (minimum 11 for each tone—assessed via the Fitzpatrick Scale [29]).	Suffering from skin conditions (e.g., eczema).
Healthy groups only: physically active (i.e., performing exercise 1 to 3 times a week).	Under drug therapy affecting thermoregulation (e.g. muscarinic antagonists).
SCI group only: presenting thoracic injury/paraplegia (i.e., injury level within T1-S1).	Smoker or Vaper.
SCI group only: >12 months post-injury and no history of PUs.	

As identified by the “Guidelines for the conduct of clinical trials for spinal cord injury as developed by the ICCP Panel” [30], inclusion and exclusion criteria for SCI participants should consider the confounding effects of various independent variables such as pre-existing or concomitant medical conditions, other medications, surgical interventions, and rehabilitation regimens. As it may not be practical or justifiable to limit study enrolment based on factors such as e.g., rehabilitation regime or sex, all potentially confounding factors will be comprehensively recorded and considered as potential co-variables in primary and secondary data analyses.

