## Measurements

### Skin blood flow

Continuous skin blood flow will be monitored via Laser Doppler Flowmetry at the sacrum.

LDF is a non-invasive technique that uses optical probes to measure blood flow velocity in the microvasculature. Typically, tissue thickness is sampled at 1mm implementing the Doppler principle whereby light from a monochromatic laser becomes scattered from moving red blood cells, allowing it to be applied to a wide range of anatomical locations [33]. Given its relative low cost and ease of use, LDF is validated [34] and has been widely used to assess changes in blood flow velocity (as an index of changes in flow) over bony prominences, such as the sacrum [6, 13–15, 35].

The optical probe is integrated within the custom-built temperature probe, allowing concurrent manipulation of skin temperature whilst monitoring real-time changes in skin blood flow, during loaded and minimal loaded states. Blood flow during the loading phase will be analysed via spectral analysis of wavelet frequency to investigate temperature-modulated regulatory mechanisms during loading (i.e. changes in 0.1 Hz, 0.04 Hz, and 0.01 Hz frequencies will be associated with myogenic activity of vascular smooth muscles, neurogenic activity of the vessel wall, and vascular endothelium related metabolic activity, respectively) [11]. Blood flow during the minimal loading phase will be used to calculate the baseline skin blood flow (taken as the mean average during the final 3-minutes of the 10-mintue baseline period). The average baseline will then be used for normalisation of peak hyperaemia [(peak hyperaemia—average baseline skin blood flow)/average baseline skin blood flow)*100)] to investigate its modulation via cooling. Changes in peak hyperaemia represent a robust and repeatable microvascular response [36], which is directly implicated in the pathophysiology of PUs [36]. Secondary perfusion parameters will include the time to peak hyperaemic response and the perfusion area between the skin blood flow response curve and the mean baseline skin blood flow after unloading and during the reperfusion phase. In the measurement of peak hyperaemia skin blood flow will be collected continuously (40 Hz sampling rate) and averaged every 1-minute for the analysis of the temporal dynamics of cooling induced changes in skin blood flow under loading.

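### The effect size f = 0.4 comes from a two-condition contrast without groups, so 80% power is not established for the group-by-temperature interaction, and 18 per group does not follow from the stated inputs

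*Protocol article*

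**What the plan says.** Under Participants, the sample size is computed "with an effect size f = 0.4 for a repeated-measure ANOVA", with the settings "within-between interaction; α = 0.05; β = 0.80; 3 groups; 3 measurements". The data behind it are peak hyperaemia "during control conditions (32.7 ± 9.4% CVCmax) and during sensory nerve block (17.3 ± 6.8% CVCmax"), that is, percent of maximal cutaneous vascular conductance. The article argues that cooling should act much like the nerve block and that the roughly 50% reduction "was a large (f = 0.4) and physiologically meaningful effect size to evaluate the beneficial effects of cooling on sustained mechanical loading". It concludes that at least 18 participants per group are needed and sets 35 per group to allow for up to 50% dropout.

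Under Skin blood flow, the endpoint is on another scale, percent change from baseline flow: "The average baseline will then be used for normalisation of peak hyperaemia".

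The Introduction gives two aims: how levels of cooling change the skin's responses (Aim 1), and how ageing and spinal cord injury (SCI) modify the benefit of cooling (Aim 2). Statistical analyses plans a two-way mixed ANOVA of temperature by group.

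**The concern.** The test selected is the "within-between interaction", which asks whether the cooling effect differs between young, older and SCI participants. The effect size is defended as the size of the cooling effect itself, which is the temperature main effect. The article assumes nothing about how that effect varies between groups, so nothing links the cited data to the test that was powered.

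Nor does 0.4 follow from the cited figures as a main effect. A percentage reduction is not a standardised effect; 0.4 is the value the article itself labels large.

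This paragraph is the article's only sample-size justification for the primary outcome, and it accepts shrinkage to about 18 completers per group. With that number, a null interaction could be read as an adequately powered negative answer to Aim 2 when the article gives no basis for that reading.

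**Working it through.** **Inputs from the documents.** Control 32.7 ± 9.4 and block 17.3 ± 6.8 %CVCmax; f = 0.4; alpha 0.05; 3 groups; 3 measurements; 18 and 35 per group (N = 54 and 105). The printed β = 0.80 is read as power 0.80.

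**Assumptions, not in the article.** ± is an SD. The within-person correlation ρ is 0.5, or the range shown. Sphericity ε = 1 unless stated.

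**1. The article's own figure.** For the interaction, λ = f²·N·3·ε/(1−ρ), with df 4ε and 2(N−3)ε.
- N = 18 in total, ρ = 0.5: λ = 0.16 × 18 × 3/0.5 = 17.28, df 4 and 30, power 0.885. N = 15 gives 0.796. The requirement is therefore 18 in total, 6 per group.
- At ρ = 0 the requirement is 30 in total, 10 per group.
- At N = 54 (18 per group), power is 98.9% at ρ = 0 and over 99.9% at ρ = 0.3 and 0.5.
- Two alternative effect-size conventions in the same program require 45 and 42 in total (15 and 14 per group), with power of 90% and 92% at N = 54.

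No interaction variant tried with f = 0.4 and power 0.80 gives 18 per group.

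**2. The effect size in the cited data.**
- Difference: 32.7 − 17.3 = 15.4, a reduction of 15.4/32.7 = 47%.
- Pooled SD: √((9.4² + 6.8²)/2) = 8.20.
- d = 15.4/8.20 = 1.88, so f = d/2 = 0.94 for two conditions.
- For three temperatures, f = 15.4 × s(t)/8.20, where s is the population SD of the fraction t of the effect reached at 38, 24 and 16 °C. For t = (0, ½, 1), s = 0.408 and f = 0.77. For t = (0, 1, 1), s = 0.471 and f = 0.88.

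**3. Illustrative interaction sizes.** Let group i keep a fraction g of the cooling effect. The double-centred cell means are 15.4·(g − mean g)·(t − mean t), so f(int) = 15.4·s(g)·s(t)/8.20. With young and older participants at g = 1 and SCI at g = 0, s(g) = 0.471. Then f = 15.4 × 0.471 × 0.408/8.20 = 0.36 for the linear t, and 15.4 × 0.471 × 0.471/8.20 = 0.42 for the full effect at 24 °C. A half loss halves these values and a quarter loss quarters them.

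Power, with ρ from 0.3 to 0.7 and both temperature patterns:

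| SCI keeps | f(int) | 18 per group | 35 per group |
|---|---|---|---|
| none of the effect | 0.36 to 0.42 | over 99% | over 99% |
| half | 0.18 to 0.21 | 55 to 98% | 88 to over 99% |
| three quarters | 0.09 to 0.10 | 16 to 44% | 29 to 77% |

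For the half-loss row at 18 per group and ρ = 0.5, power is 72% under the linear pattern and 85% under the other.

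**4. Smallest interaction f with 80% power.**

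| | ρ = 0.5 | ρ = 0.3 |
|---|---|---|
| 35 per group, ε = 1 | 0.14 | 0.165 |
| 18 per group, ε = 1 | 0.20 | 0.23 |
| 35 per group, ε = 0.75 | 0.15 | 0.18 |
| 18 per group, ε = 0.75 | 0.22 | 0.26 |

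**The case against.** The strongest reply is that the design is generous. For the temperature main effect, 0.4 is well below what the cited data imply, so the error is on the safe side there. Recruitment is nearly twice the stated minimum, and 35 per group detects an interaction of about 0.14 to 0.17. Even 18 per group exceeds 80% power in some half-loss scenarios. All of this stands, and it is why the sample size need not change.

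Two further replies also hold. Cohen's f has no units, so the difference between %CVCmax and percent change from baseline makes the borrowed value uncertain rather than invalid. The same difference limits the interaction sizes above, which reuse the cited SD and are only illustrations. Also, the article does not say whether ± is an SD or a standard error. If it were a standard error from about 5 or 6 participants, f would be near 0.4 (0.94/√5.5 = 0.40), but nothing in the text says so, and the value would still describe a two-condition contrast.

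None of this supplies an assumption about how the cooling effect differs between groups, and none explains the 18 per group.

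**Conclusion.** The sample-size basis is wrong as written, in two respects. First, f = 0.4 is attached to the interaction but rests on data that bear only on the temperature main effect, so the 80% power is not established for Aim 2. Second, 18 per group does not follow from the stated inputs: with correlation 0.5 about 18 in total suffice, and 18 per group gives over 98% power for f = 0.4 under the default parameterisation (90 to 92% under the two alternatives).

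A reader might infer that the trial is underpowered for Aim 2, or that 18 completers per group are too few. The documents do not support that. They state no interaction pattern and no correlation, and the illustrative power at 18 per group runs from 16% to over 99% depending on both. At 35 per group, power falls short only for small modification of the effect, such as a quarter loss in SCI. The first conclusion needs only the article's text. The sizes rest on ± being an SD, the cited SD carrying over to the endpoint, the assumed patterns, correlations of 0.3 to 0.7 and sphericity.

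**What to change.** Keep 35 per group and rewrite the paragraph:

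- Limit the cited comparison to the temperature main effect. Give its implied size (0.77 to 0.88 over three temperatures if ± is an SD), and note that 0.4 is conservative there.
- Correct or explain the 18 per group: give the correlation, sphericity and effect-size convention used, and write power (1 − β) = 0.80.
- State interaction power separately, as a detectable effect at 80% power. Under sphericity this is f of about 0.14 (correlation 0.5) to 0.17 (correlation 0.3, rounded up from 0.165) at 35 per group, and 0.20 to 0.23 at 18 per group. With ε = 0.75 it is 0.15 to 0.18 and 0.22 to 0.26.
- Use SDs of the percent-of-baseline endpoint if the pilot testing recorded them. The article says the pilot is complete, but not that such SDs exist.

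The cost is a text change, with no added participants and no change to procedures, endpoint or analysis. The claim for 18 completers per group becomes less favourable.
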